## EXPERIMENTAL METHODS

### PROCEDURES PERFORMED AT THE MIAMI VAMC

Adverse Event recording: We will record information about respiratory symptoms and other potential adverse events. Patients will also receive weekly calls to gather information about tobacco smoking abstinence, symptoms and potential adverse events.

Pulmonary function testing (PFT) will be performed according the American Thoracic Society (ATS) recommendations (52). Participants will be asked to refrain from using short-acting bronchodilators for at least 4 hours before testing if applicable. Lung volumes and  $D_LCO$  will be performed following ATS recommendations (53, 54). Height, weight and oxygen saturation will be measured prior to these tests.

Carboxyhemoglobin (COHb) will be measured in venous blood samples by co-oximetry (pHOx®ULtra, Nova Biomedical, Waltham, MA). Exhaled Carbon Monoxide (ExCO) will be measured by the handheld Smokerlyzer™ device (Covita, UK).

Collection of plasma: Blood samples will be collected in lavender-top tubes and transported to the Pulmonary Research Laboratory at the Miami VA. Plasma will be collected using a standard protocol. A full 8.5 mL of blood will be collected. This will produce about 2.5-3 mL of plasma. Tubes will be centrifuged at 2000-3000 RCF at 4°C for 15 min. Plasma will then be transferred in 1-mL aliquots to pre-labeled cryovials and freezed at -80°C until used. We will use to measure biomarkers and cotinine levels.

Biomarkers: We will measure relevant inflammatory and toxic metabolites in EBC and plasma, including  $H_2O_2$ , 8-isoprostane, IL-8, C-reactive protein, nicotine metabolites, coagulation markers, thiocyanate, acrolein. Subject’s consent will be obtained from participants to store residual samples after analysis for future studies.

Oral washes: Oral washes will be performed by having participants gargle with 10 ml sterile 0.9% saline. These washes will be centrifuged and stored at -80°C for future studies (i.e microbiome).

Leukosorb collection of nasal fluid: After 100  $\mu$ L normal saline will have been sprayed into the nose, a small paper will be inserted and the nostril closed with a nose clip for 2 minutes. Then, the paper will be retracted and eluted for cytokine analysis in the laboratory (56). No adverse effects are known.

[name] PI

ADVERSE AIRWAY EFFECTS OF INHALED NICOTINE FROM TOBACCO AND E-CIGARETTES

VERSION 3.3 09/28/2017

## PROCEDURES PERFORMED AT THE UNIVERSITY OF MIAMI

**Nasal potential difference (NPD) measurements:** This will be our primary outcome. Since tobacco smoke changes NPD, we will assess whether EC vapors with nicotine elicit a similar effect. Subjects will be instructed to exhale through the nose when vaping. NPD will be measured as previously described (47) and as detailed in Human Subjects. Effects on CFTR and CaCC-mediated ion transport will be evaluated. We will also collect nasal cells and lavages to measure TGF- $\beta$  levels (mRNA and protein by ELISA) and correlate these with the level of CFTR- and CaCC-mediated  $\text{Cl}^-$  conductance.

**Nasal lavages** will be performed using 10cc of normal saline will be harvested to measure inflammatory markers.

**Nasal brushings** will be performed to harvest nasal epithelial cells for assessment of mRNA changes (cytokines and other inflammatory molecules).

**Exhaled NO measurements** (breath and nasal) will be performed as a marker of inflammation.

**Plasma Cotinine levels measurements** 200ul of plasma of each study subject will be send to the **University of Miami Rosentiel Medical Science Building; Pulmonary Research Department Room # 7052.**

**Leukosorb collection of nasal fluid:** After 100  $\mu\text{L}$  normal saline will have been sprayed into the nose, a small paper will be inserted and the nostril closed with a nose clip for 2 minutes. Then, the paper will be retracted and eluted for cytokine analysis in the laboratory (56). No adverse effects are known.

The following **Table 1** outlines the timing of the above procedures in relation to study visits.

|                          |            | TRANSITION PHASE |        |        |        |                                | STABILITY PHASE |        |        |        |        |        |        |        |        |        |                         |
|--------------------------|------------|------------------|--------|--------|--------|--------------------------------|-----------------|--------|--------|--------|--------|--------|--------|--------|--------|--------|-------------------------|
| Time (weeks)             | E          | 1                | 2      | 3      | 4      | 5                              | 6               | 7      | 8      | 9      | 10     | 11     | 12     | 13     | 14     | 15     | 16                      |
| PROCEDURE                | enrollment | V1               | V2     | V3     | V4     | V5                             | V6              | V7     | V8     | V9     | V10    | V11    | V12    | V13    | V14    | V15    | V16                     |
| ICF                      | X          |                  |        |        |        |                                |                 |        |        |        |        |        |        |        |        |        |                         |
| baseline questionnaire   | X          |                  |        |        |        |                                |                 |        |        |        |        |        |        |        |        |        |                         |
| FU smoking questionnaire | X          | X                | X      | X      | X      | X                              |                 | X      |        | X      |        | X      |        | X      |        | X      | X                       |
| e-liquid refill          | X          | X                | X      | X      | X      | X                              | X               | X      | X      | X      | X      | X      | X      | X      | X      | X      | X                       |
| Ex CO                    | X          | X                | X      | X      | X      | X                              | X               | X      | X      | X      | X      | X      | X      | X      | X      | X      | X                       |
| venous COHb              | X          | X                | X      | X      | X      | X                              |                 |        | X      |        |        |        | X      |        |        |        | X                       |
| marihuana screen         | X          |                  |        |        | X      |                                |                 |        |        |        |        |        |        |        |        |        | X                       |
| NPD at UM                |            |                  |        |        |        | X                              |                 |        |        |        |        |        |        |        |        |        | X                       |
| nasal lavage             |            |                  |        |        |        | X                              |                 |        |        |        |        |        |        |        |        |        | X                       |
| nasal brush              |            |                  |        |        |        | X                              |                 |        |        |        |        |        |        |        |        |        | X                       |
| PFT                      | X          |                  |        |        |        |                                |                 |        |        |        |        |        |        |        |        |        |                         |
| Spirometry only          |            |                  |        |        |        |                                |                 |        |        |        |        |        |        |        |        |        | X                       |
| Mouth wash               | X          |                  |        |        |        |                                |                 |        | X      |        |        |        |        |        |        |        | X                       |
| plasma                   | X          | X                | X      | X      | X      | X                              |                 |        | X      |        |        |        | X      |        |        |        | X                       |
| time (weeks)             | E          | 1                | 2      | 3      | 4      | 5                              | 6               | 7      | 8      | 9      | 10     | 11     | 12     | 13     | 14     | 15     | 16                      |
| PAYMENTS                 | enrollment | V1               | V2     | V3     | V4     | V5
baseline
NPD at
UM | V6              | V7     | V8     | V9     | V10    | V11    | V12    | V13    | V14    | V15    | V16 pos
NPD at
UM |
|                          | \$0.00     | \$0.00           | \$0.00 | \$0.00 | \$0.00 | \$100.00                       | \$0.00          | \$0.00 | \$0.00 | \$0.00 | \$0.00 | \$0.00 | \$0.00 | \$0.00 | \$0.00 | \$0.00 | \$200.00                |

**Payment to participants:** Participants who complete the first 4 visits (screening phase) and qualify for first nasal sampling and NPD measurement, will receive a payment of \$100.00. After this they will enter a 12-week phase of consistent use of either EC or tobacco smoking and receive a payment of \$200.00 after completing the final visit with nasal sampling and second NPD measurement. Compensation will not be provided at every visit but rather after completion of each

[name] PI

ADVERSE AIRWAY EFFECTS OF INHALED NICOTINE FROM TOBACCO AND E-CIGARETTES

VERSION 3.3 09/28/2017

study phase to enhance the chances that the subject will successfully quit tobacco cigarettes and switch to EC. It's well known that smoking cessation is difficult and that reward mechanisms increase quitting rates. Although the payments are not "rewards", the payment schedule can be used as a motivation to quit.

**Planned enrollment:** The study will be performed throughout a 5-year period. Recruitment of smokers unwilling to quit and smokers that will attempt to switch to EC will be recruited as follows:

| PLANNED ENROLLMENT    | YEAR 1           |    |                  |    |          |
|-----------------------|------------------|----|------------------|----|----------|
|                       | Jul - 2015 - Dec |    | Jan - 2016 - Jun |    | TOTAL Y1 |
|                       | Q1               | Q2 | Q3               | Q4 |          |
| SMOKERS NO E-CIGS     | 0                | 2  | 2                | 2  | 6        |
| SMOKERS NPD1          | 0                | 2  | 2                | 2  | 6        |
| SMOKERS NPD2          | 0                | 0  | 2                | 2  | 4        |
| POTENTIAL E-CIG USERS | 4                | 4  | 8                | 4  | 20       |
| E-CIG NPD1*           | 1                | 1  | 2                | 1  | 5        |
| E-CIG NPD2            | 0                | 1  | 1                | 2  | 4        |

\* assuming a 25% e-cig retention

|                       | YEAR 2           |    |                  |    |          |
|-----------------------|------------------|----|------------------|----|----------|
|                       | Jul - 2016 - Dec |    | Jan - 2017 - Jun |    | TOTAL Y2 |
|                       | Q1               | Q2 | Q3               | Q4 |          |
| SMOKERS NO E-CIGS     | 0                | 0  | 2                | 2  | 4        |
| SMOKERS NPD1          | 0                | 0  | 2                | 2  | 4        |
| SMOKERS NPD2          | 2                | 0  | 0                | 2  | 4        |
| POTENTIAL E-CIG USERS | 4                | 4  | 4                | 4  | 16       |
| E-CIG NPD1*           | 1                | 1  | 1                | 1  | 4        |
| E-CIG NPD2            | 1                | 1  | 1                | 1  | 4        |

\* assuming a 25% e-cig retention

|                       | YEAR 3           |    |                  |    |          |
|-----------------------|------------------|----|------------------|----|----------|
|                       | Jul - 2017 - Dec |    | Jan - 2018 - Jun |    | TOTAL Y3 |
|                       | Q1               | Q2 | Q3               | Q4 |          |
| SMOKERS NO E-CIGS     | 0                | 0  | 2                | 2  | 4        |
| SMOKERS NPD1          | 0                | 0  | 2                | 2  | 4        |
| SMOKERS NPD2          | 2                | 0  | 0                | 2  | 4        |
| POTENTIAL E-CIG USERS | 8                | 8  | 8                | 4  | 28       |
| E-CIG NPD1*           | 2                | 2  | 2                | 1  | 7        |
| E-CIG NPD2            | 1                | 2  | 2                | 2  | 7        |

\* assuming a 25% e-cig retention

|                       | YEAR 4           |    |                  |    |          |
|-----------------------|------------------|----|------------------|----|----------|
|                       | Jul - 2018 - Dec |    | Jan - 2019 - Jun |    | TOTAL Y4 |
|                       | Q1               | Q2 | Q3               | Q4 |          |
| SMOKERS NO E-CIGS     | 0                | 0  | 0                | 2  | 2        |
| SMOKERS NPD1          | 0                | 0  | 0                | 2  | 2        |
| SMOKERS NPD2          | 2                | 0  | 0                | 0  | 2        |
| POTENTIAL E-CIG USERS | 8                | 8  | 8                | 8  | 32       |
| E-CIG NPD1*           | 2                | 2  | 2                | 2  | 8        |
| E-CIG NPD2            | 1                | 2  | 2                | 2  | 7        |

\* assuming a 25% e-cig retention

|                       | YEAR 5           |    |                  |    |          | STUDY
TOTAL |
|-----------------------|------------------|----|------------------|----|----------|----------------|
|                       | Jul - 2019 - Dec |    | Jan - 2020 - Jun |    | TOTAL Y5 |                |
|                       | Q1               | Q2 | Q3               | Q4 |          |                |
| SMOKERS NO E-CIGS     | 0                | 2  | 2                | 0  | 4        | 20             |
| SMOKERS NPD1          | 0                | 2  | 2                | 0  | 4        | 20             |
| SMOKERS NPD2          | 2                | 0  | 2                | 2  | 6        | 20             |
| POTENTIAL E-CIG USERS | 8                | 8  | 8                | 0  | 24       | 120            |
| E-CIG NPD1*           | 2                | 2  | 2                | 0  | 6        | 30             |
| E-CIG NPD2            | 2                | 2  | 2                | 2  | 8        | 30             |

\* assuming a 25% e-cig retention

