Current studies on EC vapors are conflicting and reveal that they produce either similar (19-21) or reduced (6, 22) effects on systemic nicotine levels, carcinogen levels and cardiovascular effects compared to other nicotine replacement strategies. Side effects of ECs include mouth/throat irritation (23), vertigo (23), headaches (23), bronchospasm (8, 24) and nausea (25) similar to those found with approved nicotine replacement therapies (NRT).

ECs produce nicotine vapors of a particle size that deposit the vapor in the lower respiratory tract (26, 27), unlike the larger sized particles of approved inhalation NRT devices that remain in the oropharynx (28, 29). This fact may explain why EC vaping but not NRT use has been associated with lipoid pneumonia (30) and bronchospasm (8, 24). It raises concerns that the toxicity of components of EC such as diluents may have significant health risks (31), in addition to the known risks of nicotine alone (32). The lack of consistent results demands a full evaluation of EC toxicity.

In 2009, the FDA reported that a cartridge of an electronic cigarette contained diethylene glycol (33), even though other studies failed to identify this substance. The FDA testing also identified

[name] PI

ADVERSE AIRWAY EFFECTS OF INHALED NICOTINE FROM TOBACCO AND E-CIGARETTES

VERSION 3.3 09/28/2017

tobacco-specific nitrosamines in ECs (33). Both substances are known carcinogens. However, they can also be found in nicotine gums and nicotine inhalers (34). Other harmful substances were found as well, including acrolein (35). The French national consumer agency analyzed the vapor of ECs and found formaldehyde levels matching those from tobacco cigarettes (36). On the other hand, the test conditions did not necessarily mimic real life scenarios. Therefore, exposure systems mimicking real life situations with an appropriate evaluation of toxicity are desperately needed, especially since the use of ECs has increased dramatically in recent years. Our proposal is designed to answer this question by investigating the safety of ECs in primary cultures of normal human bronchial epithelial (NHBE) cells and in clinical trials with individuals who are non-smokers or who replace tobacco smoking with EC vaping.

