## EXPERIMENTAL APPROACH

The study will evaluate the effects of inhaling EC vapor containing nicotine when used as a tobacco replacement tool. **By using active cigarette smokers as a comparator group, the study will increase our knowledge of whether the use of ECs is more or less harmful than continuation of tobacco smoking.** This study will examine the *in vivo* effects of EC vapors in nasal ion transport and TGF- $\beta$  levels as well as in serum inflammatory biomarkers.

As the primary endpoint, nasal ion transport will be assessed by nasal potential difference (NPD), which measures the voltage potential resulting from epithelial ion fluxes (both Na+ absorption and Cl and K+ secretion, see 37, 38) at the mucosal surface *in vivo*. In normal airway epithelia, Na+ absorption is the primary ion transport activity so that the resulting airway surface potential difference is negative with reference to the interstitium (39). Ion transport across nasal epithelia is representative for findings in distal airways (40, 41).

We also believe that NPD is a reasonably sensitive and minimally invasive biomarker for this study as discussed below. We will use NPD as a primary endpoint because changes in most clinical parameters will only be seen after months or even years of exposure. For that particular reason, there is a recent surge to find alternative biomarkers that may be used as surrogate endpoints in shorter clinical trials. Since NPD directly measures the changes in ion transport expected to influence mucociliary clearance (MCC) and therefore overall outcome and since changes of NPD measurements are indirectly linked to lung function changes and MCC in trials with cystic fibrosis patients (44, 45), we believe that NPD lends itself as a reasonable surrogate for MCC for this clinical trial.

As secondary endpoints, we will also measure TGF- $\beta$  levels in nasal secretions and expression in nasal cells to correlate these with the level of CFTR and CaCC-mediated Cl conductance (CFTR is known to show decreased function with elevated TGF- $\beta$ ) (42, 43). In addition plasma

samples will be collected to study systemic markers of inflammation as well as toxic substances that may result from vaping and smoking

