#### EXPERIMENTAL DESIGN

The design is a smoking replacement trial, in which we will compare changes in upper airway ion transport and inflammation in smokers who switch to EC vaping versus subjects that continue to smoke tobacco cigarettes. In addition, we will use the trial design to evaluate the feasibility of using the EC as a means to quit tobacco use.

*Study population/recruitment.* We plan to study the effects of continuous EC vaping (3 months) in 30 active smokers that successfully switch to ECs (a smoking replacement trial). For this, we plan to enroll approximately 200 active smokers (screening phase), expecting that only one fourth will be able to stay abstinent from tobacco and keep exclusively vaping the ECs after a month. The 30 subjects who can remain tobacco-smoke free for the initial 4 weeks will undergo the study procedures, as >90% of them are likely to remain on ECs for the next few months (49) (as opposed to what is observed in a smoking cessation trial (48)). Twenty additional smokers who wish to continue to smoke will be enrolled as well for the comparator group. Subjects that actively smoke and have a history of at least 5 pack-years will be invited to participate. Exclusion criteria include HIV, marijuana use, COPD, asthma and other concomitant inflammatory pulmonary disorders, subjects with known pulmonary diseases including malignancies, subjects with prior thoracic surgery and subjects that used oral corticosteroids or antibiotics within the prior 3 months, subjects with allergies to study medications and subjects incapable of providing informed consent. Subjects must be in stable condition.

Subjects will be enrolled primarily in the pulmonary function test laboratory, pulmonary and primary care clinics. We will place IRB-approved advertisements in clinics if necessary. Recruitment will occur over a course of 5 years.

The study will have 4 Phases: transition, stability, weaning and surveillance.

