*Phase I: transition from tobacco use to EC (4 weeks):* After signing informed consent, all subjects entering the screening phase will have pulmonary function testing (PFT) if none available in the prior month and we will record basic demographic and social history. After obtaining an initial blood sample (plasma), we will provide and instruct the subjects how to use the EC (eVic®). The nicotine content of the “e-liquid” provided (a PG:VG mix 50:50) will match the number of cigarettes smoked a day and will vary from subject to subject (see below for calculation). We will use the 12 mg/ml concentration e-liquid. During this “transition phase” period we will assess their success of abstaining from smoking tobacco. To monitor abstinence to tobacco smoking, subjects will be seen in person weekly for measurements of exhaled CO (ExCO), and venous COHb. ExCO > 6 ppm (50) or venous COHb >1.6% (51) will be considered the result of tobacco cigarette use. In addition, we will measure urinary marijuana with a qualitative test and if positive we will exclude the subject from the study. During those visits we will assess vaping compliance by downloading the vaping history of the EC using the myVapors® software, available from the EC manufacturer and will collect data regarding potential side effects. Subjects will be encouraged to transition solely to EC within the first 4 weeks. Blood draws for biomarker assessment will be performed in each visit of this phase.

*Phase II: Stability on EC (12 weeks):* In this phase, subjects will remain on EC use for three months. In this phase, all subjects will continue to use ECs at a stable nicotine concentration for additional 12 weeks. Tobacco use abstinence will be monitored every week as in the transition phase as detailed in Table 1. High ExCO levels will be confirmed with venous COHb if necessary. Oral washes and nasal lavages will be done at the beginning and the end of this phase.

Smoker controls: 20 tobacco smokers will be directly enrolled in the “stability” phase, where they will continue to use their regular tobacco for 3 months. They will undergo nasal samplings and NPDs before and after, with monthly blood collections. After this phase, these control subjects may be re-enrolled in the study to start in the transition phase with EC.

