## EXPECTED RESULTS, POTENTIAL DIFFICULTIES, AND ALTERNATIVE STRATEGIES

The importance of this study design is that it mimics real world use of ECs. These devices are being widely promoted as an alternative form of smoking cessation with many switching to but not weaning from them. This is in part because of the unproven statement that tobacco-free products are safer and their indoor use is unregulated, which theoretically allows an increased nicotine exposure. For the trial, we chose to study the most commonly used EC type and the most frequently used e-liquid mix of PG and VG (50:50).

The effects of EC on airway TGF- $\beta$  and ion exchange are hard to predict at this point. We expect that the presence of nicotine will significantly affect NPD similar to what regular tobacco cigarettes do. If the PG:VG mix has no local toxic effects in this subacute exposure (determined in other aspects of the study), it is possible that TGF- $\beta$  levels will improve as the duration of tobacco cigarette abstinence increases (nasal samples), but nicotine could maintain these levels seen with smoking. If this is the case, it will provide valuable information that replacing regular cigarettes with EC is not less toxic or harmful as is generally perceived.

The initial phase of screening more smokers than required to complete the analysis is necessary to avoid performing semi-invasive and time consuming procedures such as NPD in subjects likely to relapse back to tobacco use, as well as to avoid the phase of dysregulated airway inflammation that may occur when smoking cessation occurs (55). Although the subjects undergoing study procedures will do so after 4 weeks of already using ECs, we expect to still detect significant differences in the data collected 3 months later if there is cumulative toxicity in the long term.

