### 1. Risks to the Subjects

A) Human Subjects Involvement and Characteristics: We will enroll active smokers older than 18 years, who actively smoke and have a smoking history of at least 5 pack-years. These subjects should not be currently using ECs but should be willing to replace tobacco cigarettes to ECs. All subjects will undergo lung function testing to exclude chronic obstructive pulmonary disease, as this condition may not only increase the risk of procedures but also impose additional inflammatory confounders. Exclusion criteria include the presence of airflow obstruction ( $FEV_1/FVC < LLN$ ), other concomitant inflammatory pulmonary disorders (i.e asthma), subjects with known pulmonary malignancies, subjects with prior thoracic surgery and subjects that used oral corticosteroids or antibiotics within the prior 3 months, subjects with allergies to study medications and subjects incapable of providing informed consent. Subjects must be in stable condition. Considering that about 75% will not be able to stay abstinent from tobacco cigarette smoking, we expect to screen 120 subjects, who meet these criteria, to be able to have 30 subjects who will complete all study procedures 3 months apart. In addition, we will enroll 20 active smokers unwilling to quit tobacco smoking but willing to undergo the study procedures using the same exclusion criteria. Since these trials will be performed at the Miami Veterans Affairs (VA) Medical Center, we expect that subjects will be >90% men, 20% Hispanic and 25% African American.

B) Sources of Materials: The following are the procedures that will be performed:

Collection of nasal lavage fluid: Nasal lavage fluid will be used to measure changes in epithelial inflammatory cytokines. The lavage will be performed using saline pre-warmed to 37°C. The subject will keep the head bent forward with the face held horizontally, while the left nasal cavity is filled with saline, using a 10 ml syringe connected to the nostril via a short tube and a nasal olive. After 5 minutes approximately 5 ml of the saline is recovered by aspiration. The samples will be centrifuged to remove cellular debris and aliquots of the supernatants stored at -20°C in microcentrifuge tubes until analysis.

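### A finding of no NPD difference between EC users and continuing smokers cannot be reported as a tobacco-like effect, because the sub-study has no estimate of tobacco's own effect on NPD

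*Protocol*

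**What the plan says.** The protocol's NPD paragraph (Procedures Performed at the University of Miami) names NPD the primary outcome and asks: "Since tobacco smoke changes NPD, we will assess whether EC vapors with nicotine elicit a similar effect". Expected Results, Potential Difficulties, and Alternative Strategies predicts the answer: "We expect that the presence of nicotine will significantly affect NPD similar to what regular tobacco cigarettes do".

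The planned contrast, in Experimental Design, is of "smokers who switch to EC vaping versus subjects that continue to smoke tobacco cigarettes". Section 1, Risks to the Subjects, sets the population: "We will enroll active smokers older than 18 years, who actively smoke and have a smoking history of at least 5 pack-years". The 20 controls enter at the stability phase, "where they will continue to use their regular tobacco for 3 months", with NPD before and after. Table 1 gives EC users an NPD at V5 and V16 only. Expected Results confirms the timing of the first: "Although the subjects undergoing study procedures will do so after 4 weeks of already using ECs".

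On whether NPD can detect smoking, Experimental Approach says: "We also believe that NPD is a reasonably sensitive and minimally invasive biomarker for this study as discussed below". The support that follows comes from cystic fibrosis trials. The text gives no NPD effect of smoking, standard deviation, repeatability or similarity margin.

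**The concern.** To call one effect similar to another, both must be known on the same scale. Tobacco's effect on NPD is the smoker value minus the unexposed value, and the sub-study observes no unexposed value. The controls' exposure does not change between their two measurements, so their change reflects drift and repeatability rather than tobacco. The EC users have no NPD while still smoking, so their response to stopping smoke is not observed either.

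What is at stake is how a null primary result is read. If EC users and smokers look alike on NPD, the protocol's wording invites the conclusion that EC acts on the airway as tobacco does. The same data would arise if NPD, as measured in this laboratory and population, did not respond to smoking.

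**Working it through.** **The plan's own figure.** The only power statement (Statistical Analysis) is >98% for TGF-β with 30 EC users and 20 smokers. It does not concern NPD. Without an effect size, SD, alpha or sidedness it can be neither reproduced nor refuted. Assuming a two-sided 5% test and the normal approximation, it implies a difference of (1.960 + 2.054) × √(1/20 + 1/30) = 4.014 × 0.2887 ≈ 1.16 SD. The point here does not depend on it.

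**What the contrast estimates.** Work in SD units, with the unexposed mean at 0, smokers at S and EC users at E. The 'similar effect' question compares E with S. The data give only D = E − S.

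| State | S | E | D |
|---|---|---|---|
| A: NPD does not respond to smoking | 0 | 0 | 0 |
| B: NPD responds, EC equals smoke | 1 | 1 | 0 |
| C: NPD responds, EC has no effect | 1 | 0 | −1 |

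A and B have the same D. A larger sample narrows the interval around D but does not separate them.

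**Size in the planned sample.** The sample sizes of 30 and 20 come from the protocol. S, E, an SD of 1 and two-sided 5% are assumptions. Simulated two-sample t-tests on final NPD (40,000 runs) were significant as follows:

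- State A: 5.1%.
- State B with S = E = 1: 5.0%; with S = E = 0.8: 4.8%.
- State C: 92%.

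The standard error of D is √(1/20 + 1/30) = 0.289 SD. The 95% interval half-width is 1.96 × 0.289 ≈ 0.57 SD (0.58 with the t quantile on 48 df). If the true difference is zero, two one-sided 5% tests reach 80% power only for a margin of about (1.645 + 1.282) × 0.2887 ≈ 0.84 SD or wider. Even formal equivalence would show only that E is close to S. It would not show that S differs from zero.

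**Using change instead of level.** Experimental Design speaks of comparing changes. If NPD is stable in both arms between the two measurements, both changes are near zero whether or not NPD responds to smoking. The change analysis does not resolve the ambiguity.

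**What an unexposed reference would add (illustration only).** Test smokers minus non-smokers with noncentral t power, two-sided 5%. With 20 versus 20 the standard error is √(1/20 + 1/20) = 0.316 SD.

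| Assumed S | 20 vs 20 | 20 vs 30 |
|---|---|---|
| 1.0 | 87% | 92% |
| 0.8 | 69% | 78% |

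With S = 0 the test is significant in about 5% of trials, so this contrast does tell states A and B apart. The smallest S detected with 80% power at 20 versus 20 is about (1.960 + 0.842) × 0.316 ≈ 0.89 SD. The number of non-smokers is assumed.

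**The case against.** The strongest reply is that the aim is comparative. The opening paragraph, Experimental Approach and Experimental Design all ask how switching compares with continuing to smoke, and continuing smokers are the right comparator for that. This stands. The 'similar' wording appears in one procedures paragraph and in the expected results, and the point is limited to those two places.

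A reader might infer that the trial has no way at all of seeing whether NPD responds to exposure. The documents do not support that. A clear difference between EC users and smokers would suggest a response, although the arms are not randomised and selection could contribute. Only a null result is ambiguous.

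A reader might also infer that the protocol would declare EC harmful on a null NPD result. In Expected Results, the remark that replacing cigarettes is not less harmful follows the sentence on TGF-β levels. It is not clearly drawn from NPD.

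The missing reference may exist elsewhere. The wider proposal plans work "in clinical trials with individuals who are non-smokers or who replace tobacco smoking with EC vaping", and the bibliography lists a study of suppressed CFTR function in cigarette smokers. However, the available text does not cite that study, and no use of non-smoker NPD data is described. Relying on outside evidence for a comparator's effect is a legitimate choice, but it would not show that this laboratory's NPD detects smoking in this population.

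Two partial substitutes fall short as planned. Optional re-enrolment of controls contrasts tobacco with EC, not with no exposure. Nicotine and cotinine are planned as adjustment variables, not as an exposure-response check.

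**Conclusion.** The point holds in a limited form. The comparison of switching with continued smoking is usable as designed. The 'similar effect' conclusion is not supported if the result is no difference, because the design contains no unexposed reference, no NPD before the switch and no stated tobacco effect on NPD. No difference is the result the protocol expects.

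That states A and B cannot be told apart follows from D = E − S and needs no numerical assumption. The percentages are illustrations: the effect sizes, SD, test level and number of non-smokers are all assumed, and a non-significant result about 95% of the time is what any comparison with zero true difference gives. The flaw concerns what may be concluded, not an arithmetical error, and it is worth correcting because it bears on the primary outcome.

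**What to change.** In the NPD paragraph and in Expected Results, replace the question of a similar effect with whether NPD in EC users differs, or is not shown to differ, from NPD under continued smoking. Report the EC-minus-smoker NPD difference with a confidence interval. State that a null result does not show a tobacco-like effect.

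Only if non-smoker NPD data obtained with the same method in the same laboratory already exist in the parent project, also report smokers minus non-smokers with a confidence interval, adjusted for age and sex, as a supportive sensitivity check. Allow the phrase 'similar to tobacco' only if that contrast shows a tobacco effect. The documents do not show that such data exist, so the first change should not wait for the second.

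The wording change costs a few sentences and a narrower claim. The optional reference needs data sharing within the collaboration. It would be non-randomised, and the non-smokers may differ from VA smokers, expected to be more than 90% men, in ways that age and sex adjustment does not remove.
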